## Abstract

**Background:**

In recent years, breast cancer treatment has taken the path toward personalized medicine. Based on individual tumor biology, therapy tailored to the particular subtype of cancer is increasingly being used. The aim here is to find the most suitable therapy for the disease. However, the success of therapy depends to a large extent on the patient’s adherence to treatment. This, in turn, depends on how the therapy is tolerated and how the treatment team cares for the patient. Patient-centered care seeks to identify and address the individual needs of each patient and to find the best form of care for that person.

**Objective:**

In order to improve comprehensive oncological care of patients with breast cancer, the ENABLE trial digitally recorded the health-related quality of life (HRQoL), adverse events (AEs), and patient satisfaction using a mobile smartphone app. The trial provided individualized responses to reported AEs and offered assistance. Additionally, it assessed the impact of a patient-reported outcome–based intervention across various therapy settings.

**Methods:**

Patients with breast cancer were eligible to participate in the study before neoadjuvant, adjuvant, postneoadjuvant, or palliative systemic therapy against breast cancer was initiated at the Heidelberg, Mannheim, and Tuebingen, Germany, university hospitals. After 1:1 randomization into an intervention and a control group, HRQoL assessments were performed at six fixed time points during the therapy using validated questionnaires. In the intervention group, HRQoL was also assessed briefly every week using a visual analog scale (EQ-VAS). In cases of significant deterioration, therapy-associated side effects were assessed in a graduated manner, recommendations were sent to the patient, and the treatment team was informed. Additionally, the app served as an “eHealth companion” for education, training, and organizational support during therapy.

**Results:**

Recruitment started in March 2021; follow-up was completed in February 2024. In total, 606 patients were enrolled, and 592 patients participated in the study. Enrollment was completed in September 2023, and the last visit was in February 2024. The first results are expected to be published in Q2 2025.

**Conclusions:**

Participation in the intervention group is expected to improve treatment satisfaction, adherence, detection, and timely treatment of critical AEs. The close-meshed, weekly, brief HRQoL assessment will also be tested as a screening tool to detect relevant side effects during therapy. The study offers a more objective HRQoL assessment across treatment strategies.

**Trial Registration:**

Deutsches Register Klinischer Studien DRKS00025611; https://drks.de/search/en/trial/DRKS00025611

**International Registered Report Identifier (IRRID):**

DERR1-10.2196/69855

## Introduction

Breast cancer is the most common cancer in women worldwide and the fifth leading cause of cancer-related deaths [1]. In recent years, oncological therapy, in general, and treatment of breast cancer, in particular, have taken the path toward personalized medicine [2]. Current treatment of both primary and advanced breast cancer is individualized and tailored to each patient’s tumor subtype and needs. The aim here is to find the most suitable therapy. However, the success of therapy depends to a large extent on the patient’s adherence to treatment [3,4]. This, in turn, depends on how the therapy is tolerated and how the medical team cares for the patient [5]. One approach is to personalize patient care overall. Therefore, a patient’s individual needs must be identified and taken into account with the aim of finding the best form of care for each person. Patient-centered care “is respectful of and responsive to individual patient preferences, needs, and values, and ensuring that patient values guide all clinical decisions” and has been proven to be an important predictor for patient satisfaction and treatment outcomes [6].

One approach to assess these needs is to evaluate the patient’s health-related quality of life (HRQoL) during therapy. They can be measured with the help of questionnaires. A distinction is made between disease-specific and generic (cross-disease) quality of life (QoL) questionnaires [7]. The gold standard for recording HRQoL is patient-reported outcomes (PROs) [8]. PROs describe the collection of health and health care data by the patients themselves, without interpretation by physicians or other health care providers [9]. This information can include symptoms, functional status, QoL, and quality of care. As patients directly transmit these data, side effects and losses in QoL that are not queried or underestimated by the medical staff are recorded in an unfiltered process.

PROs have proven to be a useful tool both for detecting adverse events (AEs) in the context of studies and for investigating HRQoL, treatment, and care. In particular, in drug trials, PRO-AEs represent the gold standard for measuring side effects [10]. Studies have shown that practitioners generally underestimate a large proportion of the relevant side effects or do not notice them at all [11,12]. By recording PROs, precision in monitoring therapy can thus be increased. This more relevant information on treatment, in turn, contributes to improving therapy quality and patient satisfaction [13].

PROs can be collected electronically, generating information about health status in real time both for the patients themselves and for the treatment team and offering the possibility to communicate in both directions, that is, information for the treatment team and feedback to the patients [12,14]. This provides immediate feedback, and interventions can be established if the results of the ePRO survey prove to be abnormal or critical. Studies have shown that this improves symptom control [15,16], offers improved doctor-patient communication [17,18], and increases patient well-being and satisfaction [19,20]. Basch et al [12,21] attracted particular attention with their work on ePROs in patients with cancer, as he was able to show that electronic patient-reported outcome measurement not only significantly improves HRQoL but also reduces emergency room visits and even improves overall survival in patients with metastatic cancer disease [12,21]. These results were confirmed in another study in patients with advanced lung cancer [22].

In the context of patient-centered care, PROs can represent an important component in clinical routine, comparable to laboratory values, in order to give the patients’ HRQoL more weight in making decisions about treatment [7]. They can help stratify the side effects of the individual patient, make them more objective, and relate them to comparison groups.

Despite the positive outcomes of PRO-based interventions in patients undergoing metastatic (breast) cancer therapies, their impact in the neoadjuvant and adjuvant settings remains unclear. However, initial evidence suggests that PRO-supported monitoring may also have beneficial effects on HRQoL and in preventing AEs in these treatment contexts [23]. The available data, particularly regarding adjuvant therapy in patients with breast cancer, are still limited, and PRO-based interventions have not yet demonstrated a clinically significant effect [24].

The ENABLE study was designed to systematically evaluate HRQoL and AEs in patients with invasive breast cancer using digital questionnaires through the specially developed smartphone app “ENABLE.” By implementing targeted interventions, the study aimed to improve treatment satisfaction and HRQoL across various therapy settings. Additionally, it sought to examine the impact of PRO-based monitoring on patients receiving neoadjuvant and adjuvant chemotherapy and to determine whether findings from metastatic settings could be applied to these treatment phases.

## Methods

### Study Design

Patients were included before starting systemic therapy for breast cancer in neoadjuvant, adjuvant, postneoadjuvant, and palliative treatment settings. Patients were recruited at the respective oncology centers. The study randomized patients 1:1 into an intervention and a control group. In both groups, QoL was assessed for at least six fixed time points during therapy using European Organization for the Research and Treatment of Cancer Quality of Life Questionnaire-C30, European Organization for the Research and Treatment of Cancer Quality of Life Questionnaire-BR45, and Patient-Reported Outcomes Measurement Information System-29 (PROMIS-29; Figure 1). Participating centers are the university hospitals of Heidelberg, Tuebingen, and Mannheim, Germany.

**Figure 1 figure1:**
[figure not shown]
Timepoints of questionnaire assessments (visits) depending on the therapy and therapeutic strategy. Adj. CT: adjuvant chemotherapy; Adj. ET: adjuvant endocrine therapy; CT: chemotherapy; EoCT: end of chemotherapy; NACT: neoadjuvant chemotherapy; OP: operation; POST-NACT/pNACT: postneoadjuvant chemotherapy.

### Intervention Group

In the intervention group, a brief weekly assessment of the current HRQoL was additionally carried out via the app using a visual analog scale (EQ-VAS). The EQ-VAS was used as a screening tool, as previous research has demonstrated its sensitivity in detecting deterioration of HRQoL at an early stage [25]. If significant deterioration (EQ-VAS value <50 or a decrease of 10% in comparison to the last EQ-VAS value) in the current HRQoL was discovered in the intervention group, a digital questionnaire was started, which asked about therapy-associated side effects in a graduated manner (ePRO symptom query based on the Common Terminology Criteria of Adverse Events stratification), that is, classified according to symptom severity, and the treatment team was informed; this so-called reactive PRO assessment (RPA) is depicted in Figure 2. Furthermore, a graduated psychological assessment was conducted using Patient Health Questionnaire-8, Generalized Anxiety Disorder 7, and the European Organization for Research and Treatment of Cancer Quality of Life Questionnaire for Cancer-related Fatigue. In addition, the patients were presented with evidence-based educational information via the app on how to deal with the side effects as learning content, and if the side effects were more severe, they were asked to contact the treatment team. In parallel, the treatment team was informed via a web app (“PIA”), and depending on the severity of the complaints, the patient was contacted directly. Figure 3 illustrates the RPA procedure.

**Figure 2 figure2:**
[figure not shown]
Study design of the ENABLE trial: upon patient enrollment in the care portal, randomization is performed automatically using centralized block randomization. ePRO-CTCAE: electronic patient-reported outcome Common Terminology Criteria of Adverse Event; HRQoL: health-related quality of life; PRO: patient-reported outcome; PROMIS-29: Patient-Reported Outcomes Measurement Information System-29; QLQ-BR45: European Organization for the Research and Treatment of Cancer Quality of Life Questionnaire-BR45; QLQ-C30: European Organization for the Research and Treatment of Cancer Quality of Life Questionnaire-C30; R: 1:1 randomization; RPA: reactive patient-reported outcome assessment.

**Figure 3 figure3:**
[figure not shown]
(A) RPA procedure with HRQoL screening via EQ-VAS, (B) symptom query, and psycho-oncological screening in case of a value <50 or a decrease of 10 % in comparison to the last EQ-VAS value. The symptom query is followed by (C) care advice, (D) an alarm for the care team via the “PIA” platform, and (E) educational content for the patient via the app. The images show the app representations for the patient. centralized block randomization. PRO-CTCAE: patient-reported outcome Common Terminology Criteria of Adverse Event; HRQoL: health-related quality of life; RPA: reactive patient-reported outcome assessment.

### Patient Empowerment

Each patient had an individual treatment and care plan that was mapped via the app. Via a content library in the app, all study participants were provided with information about care offers, such as self-care practices for managing side effects, nutritional counseling, social counseling, physiotherapy, and sport offers, and with patient-centered, evidence-based educational information. Depending on the respective therapy and the individual situation of the patients, this information was displayed as a feed on the app’s home screen. In addition, the app provided an overview of the current status of the therapy and displayed the next appointments at the center via a calendar.

The smartphone app “ENABLE” was thus a bidirectional communication platform with an additional educational guide. This enabled patient education, and thus, patient empowerment on the one hand, and risk assessment, therapy control, and systematic QoL assessment on the other (Figure 4). The questionnaires and guides were individually adapted to the respective therapy situation and patient needs.

**Figure 4 figure4:**
[figure not shown]
The home screen of the ENABLE app with representation of the different functions. ePROM: electronic patient-reported outcome measurement.

### Care Team Web App

The treatment team of the respective study center had access to the web-based care team platform “PIA,” developed and provided by the Center for Innovative Care and the Institute of Women’s Health GmbH, via which the patients were included in the study and assigned to a treatment and care plan. The PRO data for each patient were visualized via the platform and alarms in the intervention group were displayed. In addition, the calendar could be set and the clinical data entered.

### Aim

The study aims to improve therapy adherence, recognize and treat critical side effects in a timely manner, and make the HRQoL more objective in the context of different therapy strategies. The study is intended to test the overall benefit and added value of an electronic therapy companion and to increase patient satisfaction.

### Primary Hypothesis and Outcome

The primary end point of the study is to compare HRQoL and treatment satisfaction (measured by the PROMIS-29) between the intervention and control groups.

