### Secondary Hypotheses and Outcomes

Participation in the intervention group is expected to improve treatment satisfaction, therapy adherence, and detection and timely treatment of critical AEs. The close-meshed, weekly, brief HRQoL assessment was tested as a screening tool to detect relevant side effects during therapy. The study provides HRQoL objectivity across treatment strategies. In addition, a usability and feasibility analysis of the app and the intervention concept was carried out.

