### Data Acquisition and Management

The study is based on the principles of the Declaration of Helsinki. The study plan and all other study-relevant documents were approved by the ethics committees of the university medical faculties of Heidelberg, Mannheim, and Tuebingen, Germany. The current version of the study protocol is 4.2 from December 9, 2022. Protocol amendments were communicated to participating centers immediately. The study participants have the right to request information about the personal data collected from them. Participation in the study is voluntary after all study content and objectives have been declared and written consent has been given and can be terminated at any time without any disadvantages for the patient.

Patient data and clinical data are recorded pseudonymously and stored centrally in the electronic case report form (eCRF). The data were documented from the medical reports and tumor documentation of the treating center in a web-based eCRF via the study staff at the study centers. These eCRFs are stored and managed throughout the duration of the study in a secured cloud infrastructure, which was conceptualized and initiated by the Institute of Women’s Health GmbH and the three partner sites of the Center for Innovative Care in Heidelberg, Mannheim, and Tuebingen. This high-availability infrastructure guarantees and verifies individual permission rights and user roles for all participating clinicians for strict compliance with data protection regulations. For future research, all accumulated data will be transferred into the individual clinic infrastructures after the study ends, and all externally hosted data will be permanently erased. An interim analysis of the secondary end points was conducted after 50% of the patients had been included and carried out by the Institute of Women’s Health GmbH. The data monitoring committee is made up of the principal investigators from the Heidelberg and Tuebingen centers and is independent of the sponsor of the study.

The following clinical data are recorded: demographic data, Eastern Cooperative Oncology Group status, height, weight, stage of the disease, previous diseases, clinical tumor characteristics, tumor biology, staging results, therapy-associated side effects, and previous and current therapies.

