### Sample Size Calculation

The sample size was calculated according to the primary end point HRQoL (measured via the PROMIS-29). It was based on a minimal important difference of 5 points, an SD of 10 points, a power of 80%, a 2-sided significance level of 5%, and a dropout rate of 37.5%. PASS (NCSS, LLC) software was used to calculate the sample size.

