### Statistical Analysis

The primary outcomes will be examined in an intention-to-treat analysis for all randomized individuals with a mixed linear regression model. Primary analysis will be adjusted for age, therapy situation, type of systemic therapy, Eastern Cooperative Oncology Group status at enrollment, and other important confounders if necessary. The heterogeneity between the trial sites is considered through random effects (random intercept mixed model). The level of significance is set at α=5%.

All secondary outcomes will be analyzed analogously to the primary hypothesis and according to the respective outcome using further suitable statistical methods. As in the analysis of the primary outcome, the secondary hypotheses will be adjusted for relevant confounders. In addition, the heterogeneity between study centers will be considered. Secondary outcome analysis will be performed exploratively.

All statistical analyses will be planned in detail and documented in a statistical analysis plan that will be prepared before closing the database.

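### The protocol article gives treatment satisfaction two statuses, primary and secondary, so the type I error of the primary analysis is not fixed.

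*Protocol article*

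**What the plan says.** All references are to the Methods of the protocol article.

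- **Primary Hypothesis and Outcome:** the primary end point is to "compare HRQoL and treatment satisfaction (measured by the PROMIS-29) between the intervention and control groups". Two constructs are joined, and PROMIS-29 is the instrument given.
- **Secondary Hypotheses and Outcomes:** "Participation in the intervention group is expected to improve treatment satisfaction, therapy adherence, and detection and timely treatment of critical AEs". Satisfaction is named first in this list.
- **Sample Size Calculation:** the planning is for one outcome: "The sample size was calculated according to the primary end point HRQoL (measured via the PROMIS-29"). The inputs are a difference of 5 points and an SD of 10, together with "a power of 80%, a 2-sided significance level of 5%, and a dropout rate of 37.5" per cent. Satisfaction does not appear.
- **Statistical Analysis:** "The primary outcomes will be examined in an intention-to-treat analysis for all randomized individuals with a mixed linear regression model". For the error rate the section gives one figure, with no division or ordering: "The level of significance is set at α=5" per cent. Secondary outcomes are declared exploratory, and details are deferred to a statistical analysis plan.
- **Data Acquisition and Management:** "An interim analysis of the secondary end points was conducted after 50% of the patients had been included".
- **Study Design:** PROMIS-29 is one of three questionnaires used to assess quality of life. No questionnaire specific to satisfaction is named.

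**The concern.** A confirmatory claim needs one answer to the question of which variable is primary. Here satisfaction is confirmatory in one section, exploratory in the next, and absent from the planning. A reader of the results could not tell whether a difference in satisfaction, reported as a primary finding, had been prespecified as such. Nor could they tell whether a null result on HRQoL alone counts as failure of the trial.

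The interim analysis adds to this. It covered the secondary end points, and by the article's own list satisfaction is one of them. If satisfaction is also part of the primary end point, a component of the primary may have been examined halfway through enrolment. The article does not say whether that look compared the arms.

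**Working it through.** **1. Status of satisfaction, section by section**

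| Section | HRQoL | Treatment satisfaction |
|---|---|---|
| Primary Hypothesis and Outcome | primary | primary |
| Secondary Hypotheses and Outcomes | used as a screening tool and compared across strategies | secondary |
| Sample Size Calculation | the primary end point | absent |
| Statistical Analysis | 5% for plural primary outcomes | exploratory if secondary, 5% if primary |

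Satisfaction is not just another word for HRQoL: the Objective in the Abstract lists patient satisfaction as a separate item beside HRQoL and adverse events.

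**2. Error rate under each reading** (each test two-sided at 5%)

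- *HRQoL alone is primary:* one test, so 5%.
- *Both must succeed:* a false claim requires rejection of at least one true null hypothesis, so at most 5%. With no effect on either outcome, the simulated chance that both tests reject is 0.25% at correlation 0, 0.9% at 0.5 and 3.0% at 0.9.
- *Either suffices:* if independent, 1 − (1 − 0.05)² = 1 − 0.9025 = 9.75%. The upper bound whatever the correlation is 0.05 + 0.05 = 10%. Simulating correlated normal test statistics (3,000,000 draws, no effect on either outcome) gives:

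| Correlation of the two tests | 0.3 | 0.5 | 0.7 | 0.9 |
|---|---|---|---|---|
| Chance of at least one false positive | 9.5% | 9.1% | 8.3% | 7.0% |

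The correlations are assumptions, as the article gives none.

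**3. What the sample size supports**

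The article states the inputs but no planned number, so there is no figure to reproduce. By the normal approximation, n per arm = 2 × (1.960 + 0.842)² × (10/5)² = 62.8, rounded up to 63. That is 126 evaluable patients, and 126 / (1 − 0.375) = 201.6, or 202 with dropout. This is the number for one HRQoL test.

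**4. What two primary outcomes would have needed**

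- *Either suffices, 2.5% each:* 2 × (2.241 + 0.842)² × 4 = 76.0, rounded up to 77 per arm. That is 154 evaluable, and 154 / 0.625 = 246.4, or 247 with dropout.
- *Both required at 63 per arm:* power 64% at correlation 0, 69% at 0.5 and 73% at 0.8, assuming the same half-SD effect on satisfaction.
- *At the 606 enrolled:* 606 × 0.625 / 2 = 189 per arm. Power for a 5-point HRQoL difference is 99.8% at the 5% level and 99.6% at 2.5%. Requiring both outcomes gives at least 99.6%, on the same assumption about satisfaction.

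So power does not stand in the way of any of the three rules. What is missing is a single answer on which rule applies.

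**The case against.** The strongest reply is that this is a condensed journal article. It defers detail to a statistical analysis plan that is not at hand, and a decision rule for two primary outcomes is the kind of thing such a plan holds. That reply stands as far as the missing either/both rule goes: its absence here is not a fault. It does not answer the contradiction. The status of satisfaction is not left open for a later document; the article states it, in two incompatible ways.

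Three stronger readings are tempting, and the article supports none of them.

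- *That the primary error rate is not 5%.* This follows only if success on either outcome is enough, and no section says so. The sample size section, which calls HRQoL the primary end point, points to a single test.
- *That satisfaction has no instrument.* The primary end point sentence attaches PROMIS-29. What can be said is that no satisfaction-specific questionnaire is named and that PROMIS-29 otherwise appears only as a quality-of-life measure.
- *That the interim look inflated the primary error.* The article confines that analysis to secondary end points and mentions no between-arm test, stopping rule or efficacy claim. If satisfaction is secondary, the look spends no confirmatory alpha.

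Nor does the article say that several PROMIS-29 scores would each be tested with any one sufficing, so no inflation should be calculated on that basis.

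**Conclusion.** The point holds as an internal contradiction: the sections disagree on whether satisfaction is primary, and the primary type I error is therefore undetermined. The range runs from at most 5% to an upper bound of 10%, and only the either-suffices reading exceeds 5%. The upper figures assume two tests, each at 5%, with no rule in the unseen plan to restrain them. It should be settled before results are presented as confirmatory, because as published the article would let a result on either outcome be described as the primary finding. Whether the interim analysis touched a primary variable is an open question, not an established fault.

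**What to change.** 1. In Primary Hypothesis and Outcome, delete treatment satisfaction, so that HRQoL on PROMIS-29 is the sole primary end point, tested at two-sided 5%. This should be the score for which the 5-point difference and SD of 10 were set. Put primary outcome in the singular in Statistical Analysis.
2. Keep treatment satisfaction in the secondary, exploratory list and name the instrument that actually measures it.
3. State whether satisfaction, or any primary variable, was compared by arm at the interim analysis.

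The changes are to wording only. The sponsor gives up a confirmatory claim on satisfaction; no power for HRQoL is lost, because the sample size was set for HRQoL alone.

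If two primary outcomes were truly intended, the alternative is to state the either/both rule with the matching alpha. At the enrolled number and the stated dropout, a 2.5% level would still leave more than 99% power for the HRQoL difference.
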